### Economic evaluation

For each patient, utilization of health care services will be recorded prospectively, using Case Record Forms, including urodynamic testing, surgery for SUI, re-operations, medical treatment for detrusor instability, care for urinary incontinence, and care for urinary retention. By multiplying these volumes of care with unit cost prices, direct medical costs incurred by SUI during the follow up period will be calculated for each patient. For unit cost prices, national guidelines will be used (CVZ, 2004). For costs of care for urinary incontinence and urinary retention, data from the literature will be used, converted to 2006 prices. We incorporated the health related quality of life questionnaire euroqol 5D in our study to be able to calculate QALYs (quality-adjusted life-years), which is a measure of health outcome. A QALY is the change in quality of life induced by the treatment multiplied by the duration of the treatment effect and it provides the number of QALYs gained. QALYs can then be related to medical costs to arrive at a final common denominator of cost/QALY. This parameter can be used to compare the cost-effectiveness of the treatment.

### Statistical analysis

Multivariate analysis of covariance with group, centre and the baseline covariate as independent variables will be used to estimate differences in improvement of the UDI after 12 months between the groups with 95% confidence intervals. As the UDI data are likely to be skewed, data will be log transformed prior to analysis. Other variables (i.e. IIQ) will be analyzed similarly.

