### Sample size considerations

The primary outcome of this study is the improvement of UDI at 12 months after baseline. The power calculation is performed using the non-inferiority assumption. The calculation is based on registration of 600 patients in the cohort study, of whom 200 will have discordant findings. When approximately 50% of the women give informed consent for randomization, 102 women with discordant findings will be randomized (51 to each group). As based on the non-inferiority assumption, the mean improvement in UDI in both groups is expected to be 35 with standard deviation of 10. A difference in mean improvement of 5 or less is considered as non-inferior (power 80% using one-sided testing at 0.05).

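### The non-inferiority margin is 5 raw UDI points, but the primary analysis is committed to log-transformed data, whose group effect does not map to that margin

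*Protocol article*

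**What the plan says.** Under Sample size considerations the protocol article fixes the endpoint ("The primary outcome of this study is the improvement of UDI at 12 months after baseline") and the framework ("The power calculation is performed using the non-inferiority assumption"). The planning values are in UDI points: "the mean improvement in UDI in both groups is expected to be 35 with standard deviation of 10". So is the decision rule: "A difference in mean improvement of 5 or less is considered as non-inferior (power 80% using one-sided testing at 0.05"). The resulting size is "102 women with discordant findings will be randomized (51 to each group").

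Under Statistical analysis, the between-group difference in 12-month UDI improvement is to be estimated by an analysis of covariance containing group, centre and the baseline value, with 95% confidence intervals. The same section adds: "As the UDI data are likely to be skewed, data will be log transformed prior to analysis". The sentence has no condition attached. It does not say whether scores or improvements are logged, and the article gives no margin on a log or ratio scale and no route back to points. Other variables, with the IIQ as the example, are to be handled the same way.

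**The concern.** The decision rule and the planned model are on different scales. A coefficient from logged data, once exponentiated, compares geometric means as a ratio; the margin is a difference between arithmetic means. The two need not agree, because the log stretches differences among women with low values and compresses those among women with high values.

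This is the primary analysis of the primary outcome. The Economic relevance section says that confirming the no-difference hypothesis would mean urodynamics can safely be left out. If the scale, an added constant or a ratio margin has to be settled once data are in hand, that conclusion is open to challenge. If the arms differ in shape, the log analysis can also reach a different conclusion from the one the margin defines.

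**Working it through.** **1. Reproduce the plan's sample size.** Inputs, all from Sample size considerations: margin 5, SD 10, true difference 0, one-sided alpha 0.05, power 80%.

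- Normal approximation: n per arm = 2 × (1.645 + 0.842)² × 10² / 5² = 49.5, so 50.
- Noncentral t: 51 per arm, with power 80.6%. This is the stated figure.

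The 102 women therefore belong to a comparison of untransformed mean improvements.

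**2. Convert the margin to a ratio.** With control improvement c, a deficit of 5 points is the ratio (c − 5)/c.

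| c | ratio |
|---|---|
| 35 | 30/35 = 0.857 |
| 25 | 20/25 = 0.800 |
| 15 | 10/15 = 0.667 |

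Conversely, a fixed ratio of 6/7 (0.857) permits a loss of 15 × (1/7) = 2.1 points at a control mean of 15 and 50 × (1/7) = 7.1 points at 50. Only at exactly 35 does it equal 5 points.

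**3. Values with no logarithm.** If improvement is logged, women with no change or worsening have no value. Under a normal distribution with mean 35, P(improvement ≤ 0) = Φ(−35/SD): 0.02% at the planned SD of 10, 1.0% at 15, 4.0% at 20 and 8.1% at 25. The SDs above 10 are assumptions. If the score is logged, women with a score of 0 have no value. An added constant removes the gap but affects the result: in one assumed gamma version of the 30%-failure mixture discussed under the objection, the geometric-mean ratio of 12-month scores was 0.74, 0.79, 0.93 and 1.02 with constants 0.5, 1, 5 and 20.

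**4. Similar arms.** Simulations used 51 per arm, one-sided 0.05, control improvement 35 with SD 10, and improvement logged with margin ln(30/35). Non-inferiority was declared as follows.

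| Setting (assumed shape) | raw | log |
|---|---|---|
| Equal arms, gamma | 80% | 84% |
| Equal arms, normal | 81% | 76% |
| Equal arms, lognormal | 80% | 86% |
| Sling mean 30, SD 10 (at the margin) | 5% | 3% |

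So the scales largely agree when improvement is logged. Logging the score is less benign. With equal arms (assumed baseline about 55, SD 12; log of score + 1; illustrative margin ln(26/21)), the raw analysis declared non-inferiority in 85% of trials and the log analysis in 25%. That is a loss of power, not a false conclusion.

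**5. Arms of different shape.** The distributions here are assumptions, not figures from the protocol. The control 12-month UDI is gamma with mean 15. In the sling arm, 65% are near-cured with mean 6 and 35% are failures with mean 52.

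- Sling mean: 0.65 × 6 + 0.35 × 52 = 3.9 + 18.2 = 22.1.
- True deficit: 22.1 − 15 = 7.1 points, beyond the margin.

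With 51 per arm, one-sided 0.05 and gamma shapes 1 to 4, non-inferiority was declared in 3–5% of trials on the raw scale and in 48–74% on log(UDI + 1). The log margin was the ratio that 5 points represents at the control mean; counting the added constant in that ratio or not moves the result by a few percentage points.

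**6. The opposite direction.** With improvement logged and lognormal arms, take a sling arm with mean 37 and SD 25 against a control arm with mean 35 and SD 10. Sling is better on the raw mean, yet the raw test declared non-inferiority in 60% of trials and the log test in 16%.

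**The case against.** The strongest reply is that the article names its target as a difference in UDI improvement, and that a log-scale model can be converted to raw mean differences, for example by smearing or by standardisation with a bootstrap. That step, and the treatment of zeros, could sit in an analysis plan that was not available for this review. This stands in part. A reader might infer that the trial cannot test its margin at all; the documents do not support that, because a stated conversion or a justified ratio margin would connect the two. But the article states both scales outright, without condition or link, so this is a conflict between two stated rules and not merely an omitted detail.

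A reader might also infer that the log analysis will reverse the result. Under the plan's own mean and SD, with similar arms and improvement logged, it does not: the two analyses disagreed in 2–9% of trials in the gamma and normal settings. Nor does every mixture demonstrate an error. With 30% failures, the deficit is 0.7 × 6 + 0.3 × 52 − 15 = 4.8 points, which the protocol itself counts as non-inferior, so a log analysis that declares non-inferiority there is nominally right. The 35% example is needed to show a false conclusion. Its spread is also far from the plan: the between-component SD alone is 46 × √(0.35 × 0.65) = 21.9 points, against a planned improvement SD of 10.

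Finally, no raw-point margin is stated for secondary outcomes such as the IIQ, so the mismatch does not arise for them.

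**Conclusion.** The inconsistency is real and holds whatever the distributions: margin, planning values and N are in raw points, while the primary model is on a log scale with no fixed equivalent to 5 points. Its practical effect depends on what is logged and on how the arms differ. With similar shape and spread and improvement logged, it is small. With unequal shapes, a false declaration of non-inferiority is possible: 48–74% of trials against 3–5% in the assumed 7-point-deficit example. That example shows what can happen and is not a forecast. Unequal shapes are plausible, because one arm receives a midurethral sling and the other a mixture that may include medication, physiotherapy, a pessary or surgery. The point does not extend to the sample size, which is correct for the raw scale, or to the secondary outcomes.

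**What to change.** State that the primary analysis is an ANCOVA of untransformed 12-month UDI improvement with group, centre and baseline UDI. Keep centre, since the model already includes it and randomization is stratified by it. Compare the confidence limit for the adjusted mean difference with the 5-point margin at the level used for the sample size, one-sided 0.05. The limit should be named, because a two-sided 95% interval corresponds to one-sided 0.025, where 51 per arm gives 71.4% power. Deal with skewness through robust standard errors or a bootstrap interval for the raw mean difference, and keep the log analysis as a sensitivity analysis. Leave the transformation of secondary outcomes without a raw margin, such as the IIQ, as it is.

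The cost is a few sentences of wording and no new data. N = 102 stands, with power 81.1% (normal) or 80.6% (t). The alternative is to keep the log as primary with a justified ratio margin, a re-derived N and a stated rule for values that cannot be logged, which is more work.

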### Time plan for the VUSIS study

Patient recruitment began in January 2009 and is planned to continue until January 2010. The follow-up has a duration of 24 months, so will continue until January 2012. The study is conducted in cooperation with several centers ensembled in the urogynaecology consortium. Most of the clinics have disposition over a research nurse, who attributes in administration and completion of the case record forms. All data are collected web based.

### Knowledge transfer

The outcome of the study will be important for the debate on the value of urodynamics. In the current international operative practice for SUI there is a huge increase in the number of operations. Hence the value of time consuming and costly urodynamic investigations should be very clear. The study is planned to be a starting point for a doctor's thesis. The results of our study will be submitted to different national and international scientific societies such as the International Continence Society and the International Urogynecologic Association, and is planned to be published in international scientific journals.
